## Abstract

**Background:**

Acupuncture is considered to be an effective and safe treatment for obese and overweight patients, although high-quality evidence regarding the effects of acupuncture on obesity are not conclusive. The aim of the current study is to investigate the effectiveness of electro-acupuncture plus lifestyle modification for treating obese and overweight patients, in comparison with lifestyle modification alone in China.

**Methods/Design:**

To compare the effectiveness of acupuncture plus lifestyle modification, a 2-armed, controlled trial with randomization using minimization will be conducted on 150 simple obesity and overweight patients, aged 18–50 years, for a 36-week study duration. All patients will be randomly assigned to one of two groups and will receive either acupuncture plus lifestyle modification or lifestyle modification alone. Outcomes will be evaluated at baseline and at 4 weeks, 8 weeks, and 12 weeks during treatment as well as at 6-week, 12-week, and 24-week follow-up. The primary endpoint is change of body mass index (BMI) during the 12th week. Secondary endpoints are body weight; waist-to-hip ratio; biochemical tests including serum cholesterol (TC), triglyceride (TG) and high-density lipoprotein (HDL) levels; and answers to the Short Form 36 (SF-36) and the Impact of Weight on Quality of Life Questionnaire-Lite Version (IWQOL-Lite). Statistical analyses will be based on the intention-to-treat (ITT) principle. The main endpoint will be analyzed by analysis of covariance (ANCOVA), and the objective outcome results will be analyzed by logistic regression analysis. To avoid potential confounding factors, additional sensitivity analyses will be conducted following these statistical analyses.

**Discussion:**

This trial is the first to compare the effectiveness of acupuncture plus lifestyle modification for treating obesity relative to lifestyle modification treatment alone by using a pragmatic study design. We hope that the results of this study will contribute to advancing the current methodology of acupuncture trials for obesity and will facilitate the application of useful acupuncture strategies in real-world clinical settings.

**Trial registration:**

ChiCTR-TRC-12002762. The date of registration is 31 October 2012.

## Background

Obesity, defined as a body mass index (BMI) greater than 28 kg/m^2^ in China, is a serious and prominent health issue worldwide. It contributes to multiple morbidities, including coronary heart disease, type 2 diabetes, polycystic ovary syndrome (PCOS), breast cancer, colon cancer, renal cancer, and many other serious pathologies [1–4]. Currently, obesity is estimated to affect over 396 million individuals and to cause 3.4 million deaths, 3.9 % of years of life lost, as well as 3.8 % of Disability-adjusted Life-Years (DALYs) across the globe [5, 6]. Moreover, the prevalence of obese and overweight adults in China has risen to 12.0 % and 30.6 %, respectively, during 2010 [7]. In response to the sharp increase of obese and overweight individuals, numerous obesity treatments are commonly used on these patients. However, pharmacological drugs for the management of obesity and being overweight, including orlistat, lorcaserin, and the combination of phentermine and topiramate, are constantly being debated due to their side effects, such as gastrointestinal and menstrual disorders, possible liver damage, and lack of long-term safety assurance [8–10].

Acupuncture, on the other hand, originating from China and established on the framework of traditional Chinese medicine (TCM), is one of the most important alternative and complementary therapies for treating numerous diseases. While acupuncture has been practiced worldwide, the lack of high-quality clinical evidence makes acupuncture a highly controversial therapy. Based on a series of clinical studies, which showed that acupuncture at acupoints was no more effective than acupuncture at non-acupoints, some researchers have wondered whether the effect of acupuncture is only due to the placebo effect or to bias. Recently, a meta-analysis including 18,000 randomized patients in high-quality randomized control trials has manifested novel evidence that acupuncture is superior to sham acupuncture and placebo for managing chronic pain [11]. Meanwhile, a meta-analysis containing 3013 individual patients has also indicated that acupuncture can significantly reduce average body weight (95 % confidence interval (CI) of 1.72 kg (0.50–2.93 kg)) and improve obesity rates (relative risk = 2.57; 95 % CI, 1.98–3.34) compared to lifestyle modification [12]. Furthermore, the latest systematic review has shown that acupuncture is more effective than placebo or lifestyle modification to reduce body weight and has similar effects as western anti-obesity drugs but with fewer adverse effects [13]. Thus, there is an increasing tendency to use acupuncture as an adjunctive therapy based on basic lifestyle modification treatment for obesity in both western and eastern countries.

Although acupuncture’s multiple benefits have been proved by many, convincing evidence regarding the use of acupuncture for treating obesity is still limited due to the low-quality methodologies and small sample sizes. Cho et al. [12] have summarized that two thirds of acupuncture trials on obesity, drawing from a total of 31 studies, are valued as having low Jadad scores. By performing a systematic review of acupuncture and Chinese medicine on obesity, Sui et al. [13] have concluded that studies conducted within China have a lower methodological quality than those outside of China. Sui et al. also have argued that the limitations in Chinese trials include a lack of information on blinding, methods of randomization, and reasons for discontinuation. Additionally, there was little confirmatory evidence regarding the types of acupuncture offered to obese patients. Various types of acupuncture, including manual acupuncture, electro-acupuncture, auricular acupuncture, auricular acupress, electro-acupuncture plus auricular acupress, and electro-acupuncture plus lifestyle modification, are applied for daily clinical obesity treatment. Although electro-acupuncture is more frequently performed in both clinical obesity treatment and obesity experiments [12–16], so far there is no convincing evidence supporting its effectiveness in treating obesity. Hence, two pivotal questions relating to electro-acupuncture for obesity treatment have been raised. First, does electro-acupuncture plus lifestyle modification show a better effect than conventional lifestyle treatment for treating obese or overweight patients in a high-quality randomized controlled trial in China? Second, is electro-acupuncture plus lifestyle modification treatment suitable for daily clinical obesity treatment?

To address these two questions, here we are proposing a pragmatic study design. Pragmatic trials, such as comparative effectiveness trials, have been widely employed to evaluate the effectiveness of an intervention applied for the usual clinical conditions [17–19]. The advantage of the pragmatic design is that it properly suits the essence of Chinese medicine and acupuncture for its complexity and pragmatism. With the aid of the comparative effectiveness trial design, acupuncturists can perform different treatments and determine personalized acupoints by themselves in acupuncture trials [20–22]; this offers flexibility for both acupuncturists and patients, with the benefit of the clinical effects of acupuncture according to TCM doctrine. Hugh et al. [23] have recently performed a comparative effectiveness trial to compare the effectiveness of acupuncture and counseling for treating depression. This research set a successful example for the use of pragmatic trials in clinical acupuncture studies.

Herein, we designed a comparative effectiveness trial to evaluate the effectiveness of electro-acupuncture plus lifestyle modification treatment for simple obesity and overweight patients.

## Aims

The main objective of this study is to investigate the effectiveness of electro-acupuncture plus lifestyle modification treatment for simple obesity and overweight patients (assessed by BMI and body weight) in comparison with lifestyle modification treatment alone.

## Methods

### Study design

A randomized, controlled, 2-armed trial using a parallel design with a 36-week study duration for each patient will be conducted to test 2 different hypotheses:

H_0_: acupuncture plus lifestyle modification = lifestyle modification (null hypothesis) versus H_1_: acupuncture plus lifestyle modification ≠ lifestyle modification (alternative hypothesis).

To test these hypotheses, patients will be randomized into one of two groups as shown in Fig. 1.

**Fig. 1 Fig1:**
[figure not shown]
Flow chart of study

### Patients

To be included in this study, patients need to fulfill the following criteria: be male or female, aged 18–50 years old, and have a BMI ≥ 24 kg/m^2^, as diagnosed by their general physician in accordance with the guidelines of prevention and treatment for overweight and obesity in Chinese adults [24]. The patients should have failed previously to achieve their weight-loss goals through diet and exercise alone, and be willing to accept acupuncture and lifestyle modification after the explanation of risks and benefits regarding these two therapies. In addition, the ability to read and understand consent forms and questionnaires is required.

Patients will be excluded if they meet the following criteria: they have inherited obesity or secondary obesity; an endocrine disease such as a thyroid disorder, pituitary disorder, or sex gland disorder; heart disease such as arrhythmia, heart failure, myocardial infarction, or require a pacemaker; allergic or immune disease; kidney disease such as diabetic nephropathy, secondary focal segmental glomerulosclerosis, high amino transferases (alanine, aspartate > 50 U/L), or high serum creatinine (4.25 mg/dL); or are a pregnant or lactating woman. In addition, patients who have managed their weight for 1 month or have any other conditions unsuitable for this trial as evaluated by a general physician will be excluded.

All patients will be recruited in outpatient clinics of the Affiliated Hospital of Nanjing University of Chinese Medicine. Additional advertisements will be conducted in five universities in Nanjing, China. *The Handbook of Obesity* will also be printed and sent to all patients.

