#### Safety monitoring

Routine tests, including blood, urine, and stool sample analyses, electrocardiogram, and abdominal B ultrasound, will be performed on all patients before minimization. These test results will be part of the inclusion and exclusion evidence screened by a general physician. Acupuncture adverse events are defined as bleeding, fainting, hematoma, serious pain, and local infection. All adverse events, as well as managing these events, will be carefully recorded during the treatment and in the follow-up phases.

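### The creatinine value in the exclusion list, 4.25 mg/dL with no comparator, does not fit the kidney-disease clause it belongs to and adds almost no screening for unrecognised renal impairment

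*Protocol article*

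**What the plan says.** In the protocol article, Methods, Patients, the exclusion list names "kidney disease such as diabetic nephropathy, secondary focal segmental glomerulosclerosis" and continues in the same run of examples with "high amino transferases (alanine, aspartate > 50 U/L), or high serum creatinine (4.25 mg/dL". The examples are joined as alternatives. The aminotransferase limit carries a greater-than sign; the creatinine value carries none. The paragraph closes with a general exclusion for "any other conditions unsuitable for this trial as evaluated by a general physician will be excluded".

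Under Safety monitoring, blood, urine and stool analyses, an electrocardiogram and an abdominal ultrasound are done before minimization. Of these the article says: "These test results will be part of the inclusion and exclusion evidence screened by a general physician". Creatinine is not named there. The article gives no creatinine reference range, no filtration-rate criterion and no reason for the value 4.25.

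**The concern.** A laboratory limit in an exclusion list serves mainly to find disease that nobody has yet diagnosed. If 4.25 mg/dL is the point at which creatinine counts as high, a value of 2 or 3 mg/dL is not high by the protocol's own figure. Yet such a value may well indicate the condition that the sentence sets out to exclude. The number then gives the screening physician a misleading signal.

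Two other features suggest that the clause was not checked closely: the comparator is missing beside a limit that has one, and a liver test stands among the examples of kidney disease.

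At stake is the safety of individual patients with unrecognised impairment. Both arms receive advice to cut energy intake and raise activity, and one arm also has 36 electro-acupuncture sessions. The Trial status section says that recruitment is under way, so the figure may be in use now.

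**Working it through.** The article does not derive 4.25 mg/dL, so there is no calculation of its own to reproduce. The check asks what level of kidney function the value represents.

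**Inputs from the article.** Creatinine 4.25 mg/dL; patients to "be male or female, aged 18–50 years old".

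**Assumptions from outside the article.** The factor 88.4 from mg/dL to µmol/L, three creatinine-based equations for estimated glomerular filtration rate (eGFR), and the usual bands (15–29 severe reduction, below 15 kidney failure, in mL/min/1.73 m²).

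**Unit conversion.** 4.25 × 88.4 = 375.7, about 376 µmol/L.

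**eGFR at 4.25 mg/dL.** S is creatinine in mg/dL, above κ; κ = 0.9 for men and 0.7 for women.

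- CKD-EPI 2021: 142 × (S/κ)^−1.2 × 0.9938^age, × 1.012 for women. Man aged 18: 142 × (4.25/0.9)^−1.2 × 0.9938^18 = 19.7. Woman aged 50: 142 × (4.25/0.7)^−1.2 × 0.9938^50 × 1.012 = 12.1.
- CKD-EPI 2009: 141 × (S/κ)^−1.209 × 0.993^age, × 1.018 for women.
- MDRD: 175 × S^−1.154 × age^−0.203, × 0.742 for women.

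| Equation | Man, 18 | Man, 50 | Woman, 18 | Woman, 50 |
|---|---|---|---|---|
| CKD-EPI 2021 | 19.7 | 16.2 | 14.8 | 12.1 |
| CKD-EPI 2009 | 19.0 | 15.2 | 14.3 | 11.4 |
| MDRD | 18.3 | 14.9 | 13.6 | 11.1 |

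The range is 11.1 to 19.7, or about 11–20 mL/min/1.73 m². It straddles the border between severe reduction and kidney failure.

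**What lies below the printed value.** Solving CKD-EPI 2021 for creatinine at the same ages and sexes, an eGFR of 60 corresponds to about 1.1–1.7 mg/dL and an eGFR of 30 to about 2.0–3.0 mg/dL. A creatinine of 3.0 mg/dL gives an eGFR of 16.5 to 29.9 over the three equations. That is marked impairment in every case, and it would not reach 4.25.

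**Setting the parts of the clause side by side.** Kidney disease excludes by diagnosis, with the listed items as illustrations. Creatinine is one sufficient ground among several. As a cut-off, 4.25 adds exclusions only where impairment is both undiagnosed and already at about 11–20 mL/min/1.73 m².

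**The case against.** The strongest reply is that nothing in the sentence makes creatinine the definition of kidney disease. The list is illustrative and its items are alternatives, so a patient with known kidney disease is excluded at any creatinine. Behind that stands the physician's general discretion. Safety monitoring describes a physician weighing several tests, with urine analysis and ultrasound among them, not a single number applied automatically. On this view a loose sufficient condition beside a broader one is redundant, not contradictory.

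Most of this stands. A reader might infer that the renal exclusion is fixed at 4.25 mg/dL, or that the plan admits patients with known kidney disease. The wording supports neither. What remains is the patient whose impairment shows only in the blood result. There the diagnosis clause helps least and the general exclusion is discretionary, so the physician must override the protocol's own figure for high.

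A second reply is that the severity reading depends on equations and ranges the article does not give. That is correct, and it is why they are stated as assumptions; the conclusion is the same under all three equations. A reader might also infer a proven transcription or unit error. The documents cannot show that, and the missing sign could have been lost when the text was extracted, although the sign on the neighbouring limit survived. Both need a check against source.

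That aminotransferases stand under kidney disease is an editorial fault. Patients above that limit are excluded wherever it is listed.

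**Conclusion.** The point holds in a limited form. As printed, the creatinine value lacks a comparator and, read as the cut-off for high, does not fit the kidney-disease exclusion in the same sentence. Under the assumed equations it corresponds to about 11–20 mL/min/1.73 m² across the trial's ages and both sexes, so it adds almost no screening for unrecognised impairment. A wrong figure or unit is possible but not proven.

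It would be too strong to place the value deep in advanced kidney failure for everyone: for most of the men's results it lies in the severe-reduction band. It would also be too strong to claim a biased primary result. Few patients with unrecognised impairment of this degree are to be expected among adults aged 18–50 recruited for simple obesity or overweight; that is a judgement, since the article gives no prevalence. The consequence is for individual safety, and sample size and power play no part.

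**What to change.** - Verify the creatinine figure and its unit against the source document or laboratory range.
- State the comparator.
- Reconcile the limit with the kidney-disease clause so that the two parts of the criterion agree. Which value applies, and which part governs, is for the investigators and their clinical advisers; none is proposed here.
- List the aminotransferase limit as a criterion of its own, outside the kidney examples.
- Once the limit is reconciled, and not before, check the screening creatinine on file for patients already enrolled.

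The cost is one corrected line in the criteria, by amendment, and a check of existing screening records. At most a very few more screen failures would follow.

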### Minimization randomization and blinding

Minimization randomization scheme will be performed at the Nanjing Good Clinical Practice (GCP) center through three different steps according to the extending Consolidated Standards of Reporting Trials (CONSORT) statement of Revised Standards for Reporting Interventions in Clinical Trials of Acupuncture (STRICTA) [25]: sequence generation, allocation concealment, and implementation.

#### Sequence generation

Patients will be randomly allocated to one of two groups in a 1:1 ratio using a minimization procedure controlled by the GCP center. Minimization is used to balance the severity of obesity, age, and gender between the two groups. The severity of obesity is divided into 4 levels, including overweight (24 ≤ BMI < 28), obesity I (28 ≤ BMI ≤ 32), obesity II (32 < BMI < 35), and obesity III (BMI ≥ 35) [26–29]. Once the severity of obesity, age, and gender of the patients are inputted in the online software, the minimization procedure will be implemented by a skilled statistician.

#### Allocation concealment

An Email or short message service message (SMS) detailing the random numbers and group assignment will be sent directly to the study assistant from the GCP center. Acupuncturists in this trial will not recruit patients, and the group assignment cannot be changed once it has been made.

#### Implementation

All patients who meet the inclusion criteria will be enrolled by one of two independent recruiters from the outpatient clinics of the study hospital and universities. After inclusion, a study assistant will send the patient’s information, including name, gender, numerical birthday, and BMI index, to the GCP center. A random allocation sequence will be generated by the GCP center computer when it receives the minimization information. Finally, the GCP center computer will send the random numbers and the group assignment back to the study assistant by Email or SMS.

#### Blinding

The acupuncturists and nutritionists will not be blinded due to the pragmatic trial design. The statistician will remain blinded from the identity of the two treatment groups until the end of the study.

## Intervention

### Electro-acupuncture plus lifestyle modification group

#### The acupuncture prescription

The acupuncture prescription was selected by three steps: first, literature articles and systematic reviews regarding ancient acupuncture treatment for obesity were collected [12, 13, 30–32]; the frequency of acupoints for obesity was analyzed. The stomach, spleen, *Ren* meridian, ST36, ST40, ST25, SP6, CV12, CV4, and CV6 are most frequently used in obesity treatment. Subsequently, the further acupuncture protocol was discussed and developed with experts from multiple disciplines, including professional acupuncture experts, acupuncturists, nutritionists, physicians, and statisticians. LI11, LI4, CV12, ST25, CV4, ST36, SP6, and ST44 were finally selected for use based on the literature, clinical experience, and TCM doctrine.

Specifically, semi-standard acupuncture treatment will be applied in this study. The acupuncturist who performs acupuncture on patients can choose additional acupoints beyond this main acupuncture prescription according to their TCM diagnoses and experiences. In addition, standard operating procedures (SOPs) of acupuncture will be constructed according to the Revised STRICTA guidelines [25].

#### Application of electro-acupuncture

Patients allocated to the acupuncture plus lifestyle group will receive electro-acupuncture treatment as follows: a total of 7 sterile disposable stainless steel needles (diameter: 0.25 mm; length: 40 mm, Hwatuo, Suzhou, China) will be punctured unilaterally at a depth of 25–35 mm in LI11, LI4, CV12, CV4, ST36, SP6, and ST44 on the patients, and performed alternately at the next treatment. Another 2 sterile disposable stainless steel needles will be punctured bilaterally at a depth of 25–35 mm in ST25 on the patients. Acupuncture manipulation will be used to achieve the *Deqi* sensation. Transcutaneous electro-acupuncture stimulation will be then conducted at acupoints for 30 minutes using a Han’s acupoint nerve stimulator (HANS-200, Nanjing, China). The stimulation frequency will be set at 2/15 Hz, and the intensity will vary from 0.1 mA to a maximum of 2.0 mA until the needle handle begins to tremble slightly. Acupuncture treatment will be performed 3 times per week according to the patient’s convenience, and a total of 36 acupuncture treatments will be performed on the patients in the acupuncture plus lifestyle modification group. All the acupuncturists in this trial are qualified TCM doctors. They have at least 8 years of acupuncture training experience and have a Master's degree in acupuncture.

In addition, patients allocate to the electro-acupuncture plus lifestyle modification group will also receive lifestyle modification treatment combined with electro-acupuncture treatment. The lifestyle modification treatment will be identical to that used for the lifestyle modification group below.

#### Lifestyle modification group

The lifestyle modification treatment was designed by experienced nutritionists, and the treatment protocol was established before the study began. Firstly, each patient’s lifestyle, including daily nutrient intake and exercise habit, will be collected using a dietary questionnaire [33, 34] and analyzed by a nutritionist at the beginning of the study. A face-to-face nutritional consultation will be subsequently arranged for each patient, in order to tailor an individualized lifestyle treatment. The possible goal of weight reduction for each patient will be set at this face-to-face nutritional consultation. Accordingly, a 24-hour food recall diary will be used to record mean nutrient intake during 24 hours for all the patients [35–37]. Three days of food recall diaries during each week will be collected from each patient within 3 months, for the purpose of estimating nutrition intake and self-monitoring dietary food intake. Individualized nutrition and activity advice will be given to each patient in terms of their weight-loss goals and food diaries during each week. In detail, according to Dietary Guidelines for Chinese Residents [38], it will be suggested that overweight and obese patients reduce at least 300–500 kcal of their daily nutrition intake, as well as increase by 8000–10,000 steps their daily activities during treatments. Finally, a total of 12 nutritional consultations will be given to all the patients enrolled into study within the 12-week treatment period. Specifically, social network software (QQ, WeChat) will be used to establish a social network among all the patients, promoting the persistence of treatment.

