#### Outcomes

The primary outcome is the change of BMI during the 12th week after minimization. The formula for BMI is as follows:

BMI = mass (kg)/(height(m))^2^.

The BMI of all patients will be calculated at baseline; during treatment at 4, 8, and 12 weeks; and 6-week, 12-week, and 24-week follow-up [39]. The BMI reduction will be assessed by a blinded investigator from the Clinic of Nanjing University of Chinese Medicine.

The secondary outcomes are divided into objective outcomes and patient-centered outcomes. The body weight and the waist-to-hip ratio will be used as supplementary measures in combination with the BMI, and will be calculated at baseline; during treatment at 4, 8, and 12 weeks; and at 6-week, 12-week, and 24-week follow-up. In addition, TC, TG, and HDL levels also will be tested at baseline; during treatment at 4, 8, and 12 weeks to assess the metabolic changes [40]. For patient-centered outcomes, IWQOL-Lite and SF-36 are used to measure obesity-specific quality of life. The IWQOL-Lite questionnaire is a validated, obesity-specific measure, consisting of 31 items regarding the impact of obesity on physical function, self-esteem, sexual life, public distress, and work [41–43]. Patients will be asked to rank items related to obesity in 5 areas, ranging from 5 “always true” to 1 “never true”, by an independent assessor. The independent assessor will give a detailed explanation regarding every item of this questionnaire to patients before the treatment. All the patient-centered outcomes will be detected before treatment; during treatment at 4, 8, and 12 weeks; and at 6-week, 12-week, 24-week follow-up. Adverse events and serious adverse events will be recorded during the study to assess safety. By using a valid expectation questionnaire relating to acupuncture [44], participants’ expectations for acupuncture at baseline will also be assessed.

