The main challenge of this trial is to innovate a pragmatic study protocol uniting personalized acupuncture treatment with advanced research methodologies. To resolve this challenge, a dimensional study group, including a renowned acupuncture professor, skilled acupuncturists, nutritionists, clinical methodologists, physicians, and patients, was built before the study began. Each aspect of the study design was fully discussed and revised by this group. Since the populations of obese and overweight adults in China have climbed to 12.0 % and 30.6 %, respectively, both obese and overweight patients will be enrolled in this study, reflecting those who usually receive treatment for weight-loss in terms of a pragmatic design. Lifestyle modification is the cornerstone among all the obesity treatments currently available. We therefore employ acupuncture plus lifestyle modification as an intervention in this trial, facilitating the real-world clinical treatment of obesity. To evaluate patient-reported outcomes, the IWQOL-Lite questionnaire will measure the impact of obesity on dimensional aspects of life. This questionnaire has been made by researchers at Duke University and has been used successfully in many obesity trials [47–50]. To monitor the food intake of overweight and obese patients, a 24-hour food recall diary will be applied to record mean nutrient intake during 24 hours. This diary is a valid instrument for estimating nutrition intake and a beneficial tool for self-monitoring of dietary intake. It has been proved and performed in numerous nutrition researches [32–34]. Moreover, minimization will be conducted as a random procedure in this trial, avoiding possible confounding factors such as different obesity levels, gender, and age. Additionally, an Internet social network will be established and be used throughout the study, promoting the persistence of treatment for patients during treatment and follow-up phases.

As this trial refers to two clearly different treatments, blinding is hard to perform after minimization. Hence, a limitation of internal validity and multiple potential biases, including expectations of the patients and providers, may occur during this study. To minimize these potential biases, most of the outcomes in this trial are designed to be objective outcomes, such as BMI, body weight, waist-to-hip ratio, and biochemical tests.

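### The QQ/WeChat network for all patients gives unblinded controls a trial-made channel to acupuncture patients, an avoidable contamination risk that one closed group per arm would largely remove

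*Protocol article*

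**What the plan says.** The section Lifestyle modification group states that "social network software (QQ, WeChat) will be used to establish a social network among all the patients", with the aim of keeping patients in treatment. The sentence just before it says that "a total of 12 nutritional consultations will be given to all the patients enrolled into study within the 12-week treatment period", which covers both arms. Under Application of electro-acupuncture, the lifestyle component of the acupuncture arm is tied to the control arm: "The lifestyle modification treatment will be identical to that used for the lifestyle modification group below". The Discussion adds that "an Internet social network will be established and be used throughout the study" and names both the treatment and the follow-up phases. Study design gives 36 weeks per patient.

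On who the patients are, the Patients section requires them to "be willing to accept acupuncture and lifestyle modification after the explanation of risks and benefits regarding these two therapies" and to have missed their weight target in an earlier attempt with diet and exercise only.

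On blinding and expectation, the Discussion says: "As this trial refers to two clearly different treatments, blinding is hard to perform after minimization". It goes on to say that "multiple potential biases, including expectations of the patients and providers, may occur during this study". It does not mention the network as a possible source. Outcomes says that "participants’ expectations for acupuncture at baseline will also be assessed", and Analysis puts that measure into the sensitivity analyses.

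**The concern.** Controls know that they are not getting acupuncture, were willing to have it, and receive the kind of treatment that has already failed them. A network across arms lets them hear from patients who are having 36 acupuncture sessions. Three consequences are plausible:

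- **Outside acupuncture.** Some controls may obtain it elsewhere. Under intention to treat this pulls the difference towards zero, for BMI as for the other outcomes.
- **Patient-rated outcomes.** Disappointment in the control arm may affect IWQOL-Lite and SF-36, which patients rate at every visit. Blinded assessment of BMI does not protect these.
- **Withdrawal.** If disappointed controls leave more often, missingness depends on arm. Last observation carried forward can turn that into bias in either direction.

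Expectation is measured only at baseline, before any contact through the network. Adjusting for it cannot pick up what the contact changes later.

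**Working it through.** **1. Does the network span both arms?** Three statements bear on this. The network is for all patients. The sentence before it uses the same phrase for everyone enrolled. The lifestyle package is identical in the two arms. Together these make a two-arm network the natural reading. The section heading names only the control group, so an arm-specific network is possible, but it fits the other statements less well. No sentence separates the network by arm.

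**2. The plan's own sample size.** The inputs, from Sample size calculation, are a difference of 4.84 kg, SD 7.38 kg, 80 % power and 5 % significance, two-sided because the alternative hypothesis is one of inequality. Allocation is 1:1 (Sequence generation). With k = 1 in the article's formula:

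n = (1.960 + 0.842)² × 2 × 7.38² / 4.84² = 36.5, so 37 per arm (38 with the t test).

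The stated 64 per arm is not reproduced. It does fit a standardized difference of 0.5: the t test gives 63.8, so 64. The dropout step is close: 64 / 0.85 = 75.3, so 76 per arm or 152 in total, against the stated 150. The mismatch is a separate matter. It is noted here because it decides which effect size to carry forward, so both are shown.

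**3. Dilution.** Assume that a share c of controls obtains the full acupuncture effect outside the trial. The expected difference becomes d(1 − c), where d is the standardized difference. Normal-approximation power at 64 per arm is Φ(d(1 − c)√(64/2) − 1.96), with √32 = 5.657.

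| c (assumed) | Difference, kg | Power, d = 4.84/7.38 = 0.656 | Power, d = 0.5 (assumed) |
|---|---|---|---|
| 0 | 4.84 | 96.0 % | 80.7 % |
| 10 % | 4.36 | 91.6 % | 72.1 % |
| 20 % | 3.87 | 84.3 % | 61.9 % |
| 25 % | 3.63 | 79.5 % | 56.4 % |
| 30 % | 3.39 | 73.8 % | 50.8 % |

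Worked example for c = 10 % on the stated inputs: 0.656 × 0.9 × 5.657 = 3.34; 3.34 − 1.96 = 1.38; Φ(1.38) = 0.916.

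These planning inputs are for body weight, whereas the primary outcome is BMI. The proportional shrinkage applies to either; the power figures apply to BMI only if its standardized difference is similar.

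**4. Unequal withdrawal.** With 75 randomized per arm, power is Φ(d / √(1/n₁ + 1/n₂) − 1.96).

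- 15 % lost in each arm (63.75 and 63.75): 95.9 % on the stated inputs, 80.6 % at d = 0.5.
- 10 % against 30 % lost (67.5 and 52.5): 94.6 % and 77.6 %.

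Unequal withdrawal by itself therefore costs little power. If it occurs, the harm is bias through the carried-forward values, and the documents give nothing from which to size that.

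**The case against.** The strongest case on the other side has five parts.

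- **The article is condensed.** It names two platforms, does not describe one undivided chat group, and may leave group structure and house rules to the full protocol. That is fair as far as missing detail goes. But a network among all patients is something the article states, and repeats in the Discussion, so the point does not rest on silence.
- **Controls would know about acupuncture anyway.** They had both therapies explained to them, and they come from the same hospital clinics and five universities. This stands: not all contamination would be due to the network, and its own share cannot be isolated. Contaminated controls might also get less than the full effect assumed above.
- **The network may help retention.** That is its stated purpose, and it could lower dropout in both arms. This stands too, and it is why unequal withdrawal is only a possibility.
- **There are safeguards.** BMI reduction is assessed by a blinded investigator, most outcomes are objective, and withdrawals are recorded in detail. These limit measurement bias in BMI. They do not stop controls from seeking acupuncture, and they do not protect the patient-rated scales.
- **The trial is pragmatic.** That justifies open treatment and flexible care. It does not call for a link between arms that exists only because of the trial.

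A reader might go further and infer that patients will exchange allocation and results for 36 weeks, that the protocol calls expectation bias its main limitation, or that modest contamination must take power below 80 %. The documents support none of these. Exchange is made possible, not prescribed. The Discussion lists expectations among several potential biases. On the stated inputs, power stays above 80 % up to 20 % dilution.

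**Conclusion.** The point holds as an avoidable design risk. The plan most naturally sets up a network across two unblinded arms for the whole study, and the entry criteria make controls receptive to what they may hear there. The expected effect of outside acupuncture is dilution towards zero; the effect on patient-rated outcomes and through withdrawal is possible and of uncertain direction.

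The size is not given by the documents. If 10 to 20 % of controls got the full effect, the intention-to-treat difference would be 10 to 20 % smaller. Power would be about 92 to 84 % instead of 96 % on the stated inputs, or about 72 to 62 % instead of about 81 % if the true basis is a standardized difference of 0.5. The contamination share, the full effect in contaminated controls and the value 0.5 are all assumptions. The reason to act is less the size, which is unknown, than that the remedy is nearly free and keeps the retention aim.

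**What to change.** In Lifestyle modification group, replace the network among all patients with wording such as: *One closed QQ/WeChat group will be set up for each arm. Both groups will have the same moderator and the same lifestyle content. Allocation and the treatment given in the other arm will not be discussed.* Bring the Discussion sentence into line.

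Record acupuncture received outside the protocol, in both arms, at the scheduled visits (4, 8 and 12 weeks, then the 6-, 12- and 24-week follow-up), so that contamination can be reported by arm.

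The cost is a second chat group, a line in the operating procedures and one item on the visit form. The downside is that peer support becomes specific to each arm; identical moderation and content limit this. The Trial status section says that recruitment is under way, so separate groups can protect patients still to be enrolled but cannot undo contact already made. Recording of outside acupuncture can start for everyone.
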